#### Primary Outcome

We defined the primary outcome as any re-intervention or necessity for additional imaging due to insufficient intraoperative imaging or achieved reduction.

#### Secondary Outcome

Secondary outcome is measured using different specific functional outcome scores as well as nonspecific outcome tools.

### Specific Tools

The following tools used correspond to the specific fracture treated.

#### Patient-Rated Wrist Hand Evaluation

Patients operated for distal radius fractures will fill out the Patient-Rated Wrist Hand Evaluation. This 15-item questionnaire includes both a section concerning functional outcome as well as a section that analyzes the associated pain. In both sections, the items (range from 0 reflecting no pain/disability to 100) are added up and the sum is divided by two.

#### Range of Motion

Additionally the range of motion (ROM) will be measured during the outpatient clinical visits. The ROM of the wrist will be tested by measuring the palmar flexion, dorsal extension, pronation, supination, and radial and ulnar deviation.

#### Foot and Ankle Outcome Score

Patients operated for ankle fractures have to complete the Foot and Ankle Outcome Score (FAOS Score). This score was developed to assess the patient’s opinion about nonspecific ankle problems. The FAOS consists of 5 subscales that investigate pain, function in daily living, function in sport and recreation, foot and ankle-related quality of life, and other symptoms. Standardized answer options are given (% Likert boxes) and each question gets a score from 0-4. A normalized score (100 indicating no symptoms and 0 indicating extreme symptoms) is calculated for each subscale.

### Nonspecific Tool

Health status measurement will be performed using the Short-Form 36-Item Health Survey (SF-36) in all patients. The SF-36 is a patient-reported survey of the patient’s health [7]. The questionnaire includes eight different sections (ie, vitality, physical functioning, bodily pain, general health perceptions, physical role functioning, emotional role functioning, social role functioning, mental health). Each section has a scoring range between 0 and 100. The score is proportional to the outcome with the best possible result of 100.

The visual analogue scale is used on all our patients at the 6-week control. This scale ranges from 0-10 where 0 equals no pain and 10 the worst imaginable pain.

Additionally, a medical questionnaire answered by the trauma surgeon in the outpatient clinic investigates whether any signs of a complex regional pain syndrome or complications are present.

### Statistical Analysis

Statistical analysis will be carried out using SPSS, IBM Version 21. In order to answer the primary research questions, the number of re-interventions will be compared between both groups. Additionally, we will use regression *models* to try to identify risk factors for these re-interventions such as timing and duration of surgery and the experience of the surgeon.

In order to address the secondary research questions, the evaluated specific and nonspecific outcome scores will be compared between the two groups using means and standard deviation.

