**Methods:**

In a prospective, randomized controlled, open label trial based on a noninferiority design, we will enroll 332 patients. Patients will be randomized either in the control or the intervention group. The control group will be treated according to our current, standard protocol in which all patients receive a standard anterior-posterior and lateral radiograph on the first postoperative day. Patients randomized to the intervention group will be treated without a standard postoperative radiograph. All patients (N=332) will have a routine clinical and radiographic control after 6 weeks in the outpatient clinic. Primary outcome is a change in treatment plan, defined as either additional imaging or a reoperation based on the postoperative imaging. Secondary outcome measures include a 36-Item Short Form Survey, Patient-Rated Wrist Hand Evaluation, Foot and Ankle Outcome Score, Visual Analogue Scale, and the range of motion. Those questionnaires will be filled out at the 6-week outpatient control.

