### Rationale

Intraoperative radiograph documentation, if standardized and adequately performed, has the potential to assess the quality of reduction and fixation [3,4]. Consequently, the additional value of routine postoperative radiographs should be questioned [5].

Given the trend towards cost-effective medicine [6] and keeping cumulative radiation exposure in mind, it is not surprising that these standardized postoperative radiographs are under debate [8]. Despite the above, routine postoperative radiographs are still being performed in many hospitals as a standard of care. Many surgeons and radiologists argue that radiographs obtained in the department of radiology are more standardized and less biased. We therefore evaluated the frequency of changes in treatment plan due to standardized postoperative radiographs in a retrospective trial. Changes in treatment plan were defined as a deviation from the standard postoperative protocol. This included additional imaging or a revision operation.

We found in 7.2% of patients a change in the treatment plan following the evaluation of the standardized postoperative radiograph for patients operated on for distal radius or ankle fractures in 2014. These numbers are high in percentage and suggest that standardized postoperative radiographs do add to the quality of care for the patient.

On the other hand, this retrospective study had several methodological drawbacks, especially as the intraoperative radiographs performed were not standardized. Therefore, we decided to evaluate the need for postoperative radiographs using a prospective randomized control trial. We would expect a significant reduction in radiation exposure and costs of around CHF 1.3 million (estimated for employed patients in Switzerland in 2015 [9]).

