### Sample Size Calculation

We determined the sample size for both the radius and ankle fracture group after a retrospective evaluation concerning the rate of postoperative treatment plan changes. We found a rate of 7.2% changes in treatment plan after obtaining standard postoperative radiographs in 2014. Based on these findings and using a power of 0.80 and alpha failure of .05, we performed a sample size calculation.

Based on a noninferiority approach, we calculated 158 patients needed in each treatment arm. Corresponding to the standard protocol following operative fracture care, we have a standard first outpatient control after 6 weeks. Based on a separate evaluation, concerning the frequency of patients being lost to follow-up, 4.6% of our patients in 2014 did not obtain their 6-week control. Therefore we added 5% loss of follow-up to our power calculation, resulting in 158 x 1.05=166 patients in each treatment arm.

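### The two primary-outcome definitions use different triggers, and the primary analysis names re-interventions only, although the 7.2% behind the sample size also counts additional imaging

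*Protocol article*

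**What the plan says.** Four places in the protocol article bear on the primary variable.

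- **Abstract, Methods:** "Primary outcome is a change in treatment plan, defined as either additional imaging or a reoperation based on the postoperative imaging".
- **Primary Outcome:** "any re-intervention or necessity for additional imaging due to insufficient intraoperative imaging or achieved reduction".
- **Statistical Analysis:** to answer the primary questions, "the number of re-interventions will be compared between both groups". The risk-factor regression in the same paragraph also models re-interventions.
- **Rationale and Sample Size Calculation:** the planning rate comes from a retrospective series of changes in treatment plan. On what counted as a change, the Rationale says "This included additional imaging or a revision operation". The sample size section says "We found a rate of 7.2% changes in treatment plan after obtaining standard postoperative radiographs in 2014" and goes on to 158 per arm, "using a power of 0.80 and alpha failure of .05", or 166 per arm after a 5% allowance for loss to follow-up.

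The article calls the design noninferiority but states no margin, does not say whether alpha is one- or two-sided, and does not split the 7.2% into imaging and revision.

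**The concern.** There are two separate mismatches.

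**Trigger.** The Abstract and the Primary Outcome section agree on the components but not on what sets off an event. Under the Abstract, it must follow from postoperative imaging. Every control patient has a day-1 radiograph that can produce such an event. Intervention patients have none, and their only routine postoperative film is at 6 weeks. Under the Primary Outcome section, the event follows from inadequate intraoperative imaging or reduction, and the Inclusion Period section has the intraoperative images reviewed the next day. A control patient re-imaged because of the day-1 film is clearly an event under the Abstract and only arguably one under the Primary Outcome section. The between-arm difference can therefore depend on the definition used.

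**Components.** The Primary Outcome section lists re-intervention and additional imaging as separate items. In that vocabulary, an analysis of re-interventions excludes imaging. The 7.2% includes it.

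At stake is whether the primary noninferiority comparison concerns the variable on which 158 per arm and 80% power were based.

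**Working it through.** **Inputs.** From the Sample Size Calculation: p = 0.072, n = 158 per arm, power 0.80, alpha 0.05. Not given, and so assumed: equal true rates in both arms for sizing, alpha taken as one-sided (0.05, with 0.025 as the alternative), and the revision share s of the 7.2% (25%, 50%, 75%).

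**1. The plan's own figure.** With no margin stated, 158 cannot be reproduced forwards. Solving backwards:

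margin m = (z(1−α) + z(0.80)) × √(2p(1−p)/n), where √(2 × 0.072 × 0.928 / 158) = 0.02908.

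- One-sided 0.05: 2.486 × 0.02908 = 0.0723, about 7.2 points. Forwards, a margin of exactly 7.2 points gives 160 per arm, close to 158.
- One-sided 0.025: 2.802 × 0.02908 = 0.0815, about 8.15 points.

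The inflation agrees with the article: 158 × 1.05 = 165.9, so 166, and 2 × 166 = 332. Whichever margin was used, the only rate given for the calculation is the 7.2% composite.

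**2. Expected events if only re-interventions count.** Rate = s × 7.2%; events per arm = 158 × rate.

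**3. Fixed absolute margin of about 7.2 points, one-sided 0.05.** Power under equal rates = Φ(m/SE − 1.645), with SE = √(2 × rate × (1 − rate)/158). The chance of declaring noninferiority when the true rate doubles is the exact sum over two binomials (158 each) of outcomes whose upper Wald limit lies below the margin.

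**4. Margin scaled to the rate (m × s).** Same power formula, then the n needed for 80% power.

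| Revision share | Rate | Events per arm | Margin ÷ rate | Power, fixed margin | True doubling passes, fixed margin | Power, scaled margin | n per arm for 80%, scaled margin |
|---|---|---|---|---|---|---|---|
| 100% (composite) | 7.2% | 11.4 | 1.0 | 80% | 5% | 80% | 158 |
| 75% | 5.4% | 8.5 | 1.3 | 88% | 15% | 69% | 215 |
| 50% | 3.6% | 5.7 | 2.0 | 96% | 43% | 53% | 329 |
| 25% | 1.8% | 2.8 | 4.0 | >99% | 89% | 33% | 669 |

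**5. Sensitivity to sidedness.** The exact calculation at one-sided 0.025 with the 8.15-point margin gives 5%, 17%, 47% and 91% for a true doubling, in the same row order. The pattern does not change.

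**The case against.** The best defence is that re-interventions is loose shorthand for the composite. The sentence says it answers the primary research questions, and both definitions and the planning rate concern the composite. On that reading one word needs changing, and 7.2%, 158 and 80% are untouched. This may well be what was meant. It does not remove the problem, because the Primary Outcome section separates the two terms and an analyst following the text would leave out imaging.

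Several stronger readings are tempting and not supported:

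- **Three competing definitions.** There are two, with the same components. The Statistical Analysis sentence is a mismatched analysis variable, not a third definition.
- **The trial is underpowered.** With the absolute margin held fixed, power under equal rates rises as the event gets rarer. It falls only if the margin is scaled to the lower rate. What suffers under a fixed margin is protection against a relative increase in events.
- **A count is compared where a proportion was planned.** Comparing numbers between two equal arms is ordinary wording, and the exact test may stand in the full protocol or analysis plan.
- **The endpoint will be picked after the data are seen.** The trial is open label, but a fuller document may fix the variable. The article does not show otherwise.

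It is also fair to say that the doubling figures partly reflect a lenient implied margin, and that they drop quickly as the revision share rises.

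**Conclusion.** Wrong as written. The article gives two triggers for one composite, and one of them cannot operate equally in both arms. It then names an analysis variable that, taken literally, is a subset of the one behind the 7.2%. The stated 80% power at 7.2% does not describe that subset. These points rest on the text alone.

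The size does not. It depends on an assumed revision share and on a margin back-solved from 158 per arm under equal rates and an assumed sidedness. Within shares of 25% to 75%, expected events fall from 11.4 to between 2.8 and 8.5 per arm, and the chance of accepting a true doubling rises from about 5% to between 15% and 89%. The direction holds for any share below 100%; the exact figures are illustrations. A reader might infer that the investigators intend to test the rarer endpoint. The document does not establish that, only that its wording leads there.

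**What to change.** State one definition and use it unchanged in the Abstract, Primary Outcome and Statistical Analysis sections: a patient with at least one additional imaging or re-intervention, with a trigger worded so that it can occur in the same way in both arms. Make the comparison of the proportion of patients with this composite the primary analysis. Report re-interventions and additional imaging separately as its components, and say which of these variables the risk-factor regression models.

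The cost is wording in three sections and two extra rows in a results table. The 7.2% basis and 158 per arm stay as they are, and no further patients are needed. If re-interventions alone are truly intended as the primary variable, the sample size has to be justified again from a re-intervention rate and a stated margin.

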### Sample Size Calculation

We determined the sample size for both the radius and ankle fracture group after a retrospective evaluation concerning the rate of postoperative treatment plan changes. We found a rate of 7.2% changes in treatment plan after obtaining standard postoperative radiographs in 2014. Based on these findings and using a power of 0.80 and alpha failure of .05, we performed a sample size calculation.

Based on a noninferiority approach, we calculated 158 patients needed in each treatment arm. Corresponding to the standard protocol following operative fracture care, we have a standard first outpatient control after 6 weeks. Based on a separate evaluation, concerning the frequency of patients being lost to follow-up, 4.6% of our patients in 2014 did not obtain their 6-week control. Therefore we added 5% loss of follow-up to our power calculation, resulting in 158 x 1.05=166 patients in each treatment arm.

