## Abstract

**Background:**

Distal radius and ankle fractures are one of the most common operatively treated fractures. To date, there is no consensus concerning the need for a standard postoperative radiograph. This leads to undesirable practice variations. A standardized radiograph in the department of radiology would theoretically be more reproducible and operator independent than an intraoperatively obtained fluoroscopic image. However, if adequate intraoperative radiographs have been obtained, it is questionable if these postoperative radiographs are necessary and will lead to changes in the treatment strategy. If standard postoperative radiographs are no longer required, this would lead to a reduction in radiation exposure and health care costs. The hypothesis is that routine standardized postoperative radiographs do not influence the quality of care for patients operated on for either a distal radius or an ankle fracture if adequate intraoperative standardized radiographs have been obtained.

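### The 158 per arm and 0.80 power hold only for wrist and ankle fractures combined; the text should say so, and fracture type should enter the analysis and reporting

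*Protocol article*

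**What the plan says.** The Rationale gives one retrospective rate for the two fractures together: "We found in 7.2% of patients a change in the treatment plan following the evaluation of the standardized postoperative radiograph". The Sample Size Calculation section begins "We determined the sample size for both the radius and ankle fracture group" and carries the same figure forward: "We found a rate of 7.2% changes in treatment plan after obtaining standard postoperative radiographs in 2014". It continues "using a power of 0.80 and alpha failure of .05, we performed a sample size calculation" and concludes "Based on a noninferiority approach, we calculated 158 patients needed in each treatment arm". A 5% allowance for loss to follow-up raises 158 to 166 per arm. The abstract states "we will enroll 332 patients".

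The hypothesis in the abstract is that routine films "do not influence the quality of care for patients operated on for either a distal radius or an ankle fracture", given adequate intraoperative images. The Conclusion section foresees a possible change in postoperative practice after fixation of both fractures.

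In the Statistical Analysis section, "the number of re-interventions will be compared between both groups", the groups being the two randomized arms. Regression models are to look for risk factors, with timing and duration of surgery and surgeon experience as examples. The specific and nonspecific scores are compared between arms. Under Nonspecific Tool, the SF-36 and the pain scale are collected in all patients, wrist and ankle alike. Fracture type is not mentioned in the analysis text.

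**The concern.** A reader can take the opening sentence of the sample size section to mean that each fracture group was sized to 0.80 power. The numbers show otherwise, and nothing in that section says so.

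This matters because the trial joins two joints that the protocol itself handles differently. They have separate sets of intraoperative views with separate adequacy criteria, different load restrictions after surgery and different functional scores. The intervention relies on those joint-specific views, so an equal effect of omitting the film in both joints is an assumption. If a pooled result is then carried over to each joint, a shortfall in one can be diluted by no effect in the other. SF-36 and pain scores are also compared over a mixture of wrist and ankle patients, whose levels at 6 weeks may well differ.

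**Working it through.** **Inputs.** From the article: rate p = 7.2% for both fractures combined, power 0.80, alpha .05, 158 per arm, 5% inflation, 332 in total. Not stated, hence assumed: the noninferiority margin, whether alpha is one- or two-sided, the wrist:ankle split, and any fracture-specific rate. I apply 7.2% to both arms and both joints unless noted.

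**1. Is 158 pooled or per fracture?** 158 x 1.05 = 165.9, so 166; 2 x 166 = 332. That is the full enrolment, so 158 per arm covers both fractures together.

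**2. Reproducing 158.** With equal true rates, n per arm = (z(1-alpha) + z(0.80))^2 x 2p(1-p) / margin^2, where 2p(1-p) = 2 x 0.072 x 0.928 = 0.1336.
- One-sided 0.05, margin 7.2 points: (1.645 + 0.842)^2 x 0.1336 / 0.072^2 = 159.4, so 160. The margin that gives exactly 158 is 7.23 points.
- One-sided 0.025: the margin that gives 158 is 8.15 points.

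So 158 cannot be reproduced from the article's inputs alone, but these two margins fit it.

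**3. Power, pooled and for one joint.** Power = Phi(margin / sqrt(2p(1-p)/n) - z(1-alpha)), with n = 158 x the joint's share.
- Pooled, n = 158: the standard error is sqrt(0.1336/158) = 0.0291. At 7.2 points, Phi(0.072/0.0291 - 1.645) = 79.7%; at 8.15 points and one-sided 0.025, 80.0%.
- Even split, n = 79: the standard error is sqrt(0.1336/79) = 0.0411. At 7.2 points, Phi(0.072/0.0411 - 1.645) = 54.2%; at 8.15 points, Phi(0.0815/0.0411 - 1.960) = 50.9% (50.8% with the unrounded margin).

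| Split | 7.2 points, one-sided 0.05 | 8.15 points, one-sided 0.025 |
|---|---|---|
| 50:50 | 54% each | 51% each |
| 60:40 | 61% and 47% | 58% and 43% |
| 70:30 | 67% and 39% | 65% and 34% |

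At an even split, success in both joints has probability 0.542^2 = 29%, or 0.508^2 = 26%. If the joint's own rate were between 4% and 10.4% (assumed), power at n = 79 would run from 75% to 44% (7.2 points, one-sided 0.05). Expected events at 7.2% are 79 x 0.072 = 5.7 per arm per joint, and 316 x 0.072 = 22.8 overall.

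**4. Size needed for 0.80 in each joint.** 158-160 per arm per joint is 632-640 evaluable patients, or 664-672 with the factor 1.05, against 332 planned.

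**5. Dilution.** Suppose an even split, no effect in one joint, and the other worse by the full margin. The pooled true difference is then half the margin. At 7.2 points the intervention rate averages 7.2% + 3.6% = 10.8% and the standard error is sqrt((0.0668 + 0.0963)/158) = 0.0321, so the chance of passing is Phi(0.036/0.0321 - 1.645) = 30%. The same sum at 8.15 points and one-sided 0.025 gives 24%. Simulating the Wald test gives about 31% and 26%.

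**6. Precision gain from stratifying the primary outcome.** With joint rates of 4% and 10.4% (assumed, averaging 7.2%), the ratio of within-stratum to pooled variance is (0.04 x 0.96 + 0.104 x 0.896) / 0.1336 = 0.985. That is a 1.5% reduction; pooled power moves from 79.7% to 80.2%. At 2% and 12.4% the reduction is about 4%.

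**The case against.** The pooled reading is consistent throughout: one rate, one total, one two-arm randomization and one comparison between arms. The word for the fracture group in the sample size sentence is singular, and the either-or wording of the hypothesis can simply describe who is eligible. A reader might infer that the trial promised 80% power per fracture and delivers 54%. The document does not support that, since no test or power is promised for a single fracture, and 54% rests on an assumed margin, sidedness, even split and equal rates. All of this stands.

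A reader might also infer that the plan ignores fracture type. That goes too far as well. The risk factors are given only as examples, the joint-specific scores are already separated, and stratified or subgroup analyses are often left to a full protocol or analysis plan, neither of which is shown. Nor is the noise argument strong: step 6 shows that stratifying barely changes precision for the primary outcome. Differences in views and aftercare apply to both arms and do not bias the randomized comparison.

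What remains is an ambiguous sentence about what was sized, conclusions worded to reach both joints, and a pooled test that says little about either joint alone.

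**Conclusion.** The point holds as a matter of scope and wording, with an inexpensive improvement to the analysis. The 158 per arm and the 0.80 power apply to the two fractures combined. It is not a missed power target and not a flaw in the pooled comparison.

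A conclusion for one joint alone would have about 51-54% power at an even split and about 34-67% for splits up to 70:30. This assumes 7.2% in both joints and a margin of 7.2 points (one-sided 0.05) or 8.15 points (one-sided 0.025). A pooled pass would occur in roughly 26-31% of trials even if one joint were worse by the full assumed margin, so it should not be carried over to each joint. The unstated margin and sidedness are the more basic gap in the same section; every power figure here depends on filling it by assumption.

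**What to change.** - Reword the opening of the sample size section to say that 158 per arm and 0.80 power are for distal radius and ankle fractures combined. State the margin and the sidedness of alpha there.
- Make the primary estimate a risk difference stratified by fracture type (Mantel-Haenszel or stratified Miettinen-Nurminen), and include fracture type as a covariate in the SF-36, pain and risk-factor models. The gain is small for the primary outcome and possibly larger for SF-36 and pain.
- Report the wrist and ankle risk differences, each with a 95% confidence interval. This step, not stratification, is what exposes dilution.
- Claim noninferiority for a single joint only if its own interval excludes the stated margin; otherwise confine the claim to the pooled population.

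A 95% interval corresponds to one-sided 0.025. If the margin is set at 7.2 points and judged on that interval, power is Phi(0.072/0.0291 - 1.960) = 70% pooled and Phi(0.072/0.0411 - 1.960) = 42% per joint at an even split. Margin and confidence level should therefore be fixed together.

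The cost is wording and analysis code. Fracture type is part of eligibility and so known for every patient, and with 104 of 332 enrolled at publication the change could be made before analysis. The downside is that single-joint conclusions become more modest.

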### Study Population

The study includes patients operated for a distal radius or ankle fracture at a Level 1 trauma center in Switzerland. Patients presenting with these fractures at the emergency department will be eligible for study inclusion if they fulfill all of the following criteria: indication for an operation of a distal radius fracture, according to the Arbeitsgemeinschaft für Osteosynthesefragen (AO) Classification types 23-A-C [4], or an ankle (according to the AO Classification Types 44-A-C) fracture, 18 years of age or older, sufficient understanding and writing of German language, and signed informed consent. The informed consent forms will be stored by the study nurse during the trial.

Patients are excluded if they meet at least one of the following exclusion criteria: not willing/able to sign the informed consent, indication for postoperative computed tomography (CT), pathological fractures, open fractures (>grade I according to Anderson and Gustilo [11]), patients not able to attend the 6 weeks outpatient control, or missed intraoperative standardized radiographs.

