#### Inclusion Period

After sufficient information is provided to all trauma surgeons, inclusion starts. Intraoperative radiographs are obtained by the ZIEHM SOLO (Ziehm Imaging GmbH). These radiographs are saved separately in our PACS. The next day, these radiographs are evaluated by the senior surgeon of the department of orthopedics and trauma surgery and a senior radiologist. If the quality of the intraoperative radiographs is standardized and good, the patient remains in the study arm to which they were assigned.

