### Randomization

Prior to the operation, the patients are randomized to the control or the intervention group. The randomization will be carried out using a special in-hospital randomization tool. Thereafter, the patient will be included in one of the following two groups.

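### The 5% allowance covers only missed 6-week visits, although the plan also allows removal on image grounds after randomization and elsewhere treats inadequate imaging as a primary outcome event

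*Protocol article*

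**What the plan says.** All references are to the protocol article.

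- **Size.** Under Sample Size Calculation: "Based on a noninferiority approach, we calculated 158 patients needed in each treatment arm". The only loss considered is follow-up: "4.6% of our patients in 2014 did not obtain their 6-week control". This is rounded up and applied: "Therefore we added 5% loss of follow-up to our power calculation, resulting in 158 x 1.05=166 patients in each treatment arm". The Abstract gives the total: "we will enroll 332 patients".
- **Timing.** Under Randomization: "Prior to the operation, the patients are randomized to the control or the intervention group".
- **Exclusion.** The exclusion list under Study Population ends with "or missed intraoperative standardized radiographs". It also names an indication for CT after surgery.
- **Next-day check.** Under Inclusion Period, a senior surgeon and a senior radiologist review the images the day after the operation: "If the quality of the intraoperative radiographs is standardized and good, the patient remains in the study arm to which they were assigned". The text does not say what happens to the others.
- **Competing handling.** Under Intervention Group (Group II), patients whose images or reduction are not acceptable go on to further imaging or revision. Under Primary Outcome, additional imaging needed because the intraoperative images were insufficient is itself an event.

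**The concern.** Whether the standard intraoperative views were obtained can be known only during or after surgery, so that exclusion necessarily falls after randomization. The next-day quality condition falls later still. An allowance taken from clinic non-attendance in 2014 cannot cover either loss. The sponsor had reason to expect some failures: the Rationale says that intraoperative images in the retrospective study were not standardized, and the Implementation Period sets up training for that reason.

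Two things are at stake. The first is size: the 80% power belongs to 158 patients per arm, and any image-based removal comes on top of the 5%. The second matters more. The patients at risk of removal are those with inadequate images, and under the Primary Outcome section such patients may be events. Dropping them after randomization, in an open-label trial, could remove events selectively and break the comparison that randomization set up.

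**Working it through.** **Inputs.** From Sample Size Calculation: 158 per arm, 5% allowance, 4.6% observed loss, 166 per arm, power 0.80, alpha .05 (sidedness not given), reference rate 7.2%. Not in the article: a noninferiority margin and any rate of image-based removal.

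**1. The plan's own figure.** 158 × 1.05 = 165.9, rounded up to 166; 2 × 166 = 332. Both are reproduced.

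**2. What 166 leaves after follow-up loss alone.**
- At 5%: 166 × 0.95 = 157.7.
- At 4.6%: 166 × 0.954 = 158.4.

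Side note: the usual inflation divides. 158/0.95 = 166.3, so 167; 158/0.954 = 165.6, so 166. The difference is one patient per arm at 5% and none at 4.6%.

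**3. Reserve.** One removal per arm at 4.6% loss leaves 165 × 0.954 = 157.4, already below 158.

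**4. Implied margin.** With both true rates at 7.2%, the margin m that makes 158 per arm give 80% power is

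m = (z₁₋α + 0.842) × √(2 × 0.072 × 0.928 / 158)

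This gives 7.2 percentage points (0.0723) at one-sided 5% and 8.1 points (0.0815) at one-sided 2.5%. These are back-solved values, not figures from the plan.

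**5. Effect of an assumed removal share x on top of 5% loss.**

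n = 166 × 0.95 × (1 − x)

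Power = Φ(m / √(2 × 0.072 × 0.928 / n) − z₁₋α)

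Substituting m from step 4, this becomes Φ((z₁₋α + 0.842) × √(n/158) − z₁₋α). The rate and margin cancel. The result needs only that 158 gives 80%, plus the choice of alpha, and it takes the event rate as unchanged by removal. Enrolment needed to keep 158 is 158 / [0.95 × (1 − x)], rounded up.

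| x (assumed) | n per arm | Power, one-sided 5% | Power, one-sided 2.5% | Enrolment per arm to keep 158 |
|---|---|---|---|---|
| 0% | 157.7 | 79.9% | 79.9% | 167 |
| 2% | 154.5 | 79.2% | 79.1% | 170 |
| 5% | 149.8 | 78.1% | 77.9% | 176 |
| 10% | 141.9 | 76.2% | 75.7% | 185 |
| 15% | 134.0 | 74.1% | 73.3% | 196 |
| 20% | 126.2 | 71.8% | 70.7% | 208 |

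**6. The sections side by side.** For a patient with inadequate intraoperative images, Study Population (missed views) and Inclusion Period (quality condition) point towards leaving the trial or the arm. Intervention Group and Primary Outcome point towards staying, being imaged again and being counted as an event. The Inclusion Period condition is not limited to one arm, whereas the handling of unacceptable images is described only for the intervention arm.

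**The case against.** The case on the other side is substantial.

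- **The arithmetic is nearly harmless.** A reader might infer that multiplying instead of dividing makes 166 miss 158. The article does not support that: at its own observed 4.6% loss, 166 leaves 158.4, and at 5% the gap is 0.3 of a patient. This objection stands in full.
- **Removal from the analysis is not stated for poor images.** Inclusion Period says who remains and is silent on the rest; Intervention Group and Primary Outcome suggest that these patients are counted. That stands as far as it goes, but the exclusion for missed views is explicit and the quality condition has no other evident meaning. The text supports both readings and does not choose.
- **The CT exclusion may be settled before surgery.** Its timing is not given, so nothing here rests on it.
- **332 might be reached by replacing excluded patients, or the full protocol may define the analysis set.** This is possible, and such rules are often left out of an article. But the article derives 332 as 2 × 166 with follow-up loss as the only term. Replacement would also restore the number without undoing the selective removal.
- **A missed 6-week visit need not lose an early event.** This is fair: for the primary outcome the 5% may be generous, which would offset part of any removal.
- **Training should make failures rare.** That is plausible, but the article states no expected rate.

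**Conclusion.** The point holds as a conflict between the exclusion, quality-check, intervention-arm and outcome sections, together with an allowance that leaves out losses the plan permits. It is not an arithmetic error.

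The size of the loss cannot be determined from the article. On the assumptions stated, power falls by about 2 points at 5% removal, about 4 points at 10% and 8 to 9 points at 20%. A reader might conclude that the trial is shown to be underpowered. It is not: if every randomized patient is analysed, 166 per arm is adequate for the stated follow-up loss. The firmer consequence is that the text leaves open whether patients who may be primary events are dropped after randomization.

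**What to change.** Reconcile Study Population, Inclusion Period, Intervention Group and Primary Outcome so that a patient with missed or inadequate intraoperative images has one stated status in both arms. How such patients are managed clinically is for the sponsor to settle; the analysis rule can be fixed separately.

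**Preferred.** State that all randomized patients stay in the primary analysis in their assigned arm, with inadequate images handled as the Primary Outcome section defines the event and the outcome read from hospital records where a visit is missed. Only true loss to follow-up then applies, and 166 per arm can stand. The cost is more outcome ascertainment from records; no extra patients are needed.

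**If removals are retained.** Report the evaluable number as 166 × (1 − d) per arm, with d covering every permitted loss, and the power that 332 then delivers. The cost is a somewhat less favourable stated power, and the risk of selective removal remains.

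The article reports 104 of 332 patients enrolled, so either clarification could still be made well before recruitment ended.
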